Cultivating youth narratives or stories is one empowerment strategy that may facilitate empowerment and health behavior change among youth of color [25–28]. Unlike traditional didactic approaches, the development of narratives within an empowerment framework engages youth in a transformative process by recognizing knowledge embedded within their personal stories and encouraging youth to take action [19, 29, 30]. The creation and sharing of narratives thus facilitates empowerment through elaborate message processing and personalization [27]. The use of narratives within other health interventions has shown success in behavior change, including improved diet, among adults [31–35]. Results from our pilot site-randomized study of *N* = 100 parent-child pairs indicated that our narrative-based youth empowerment SSB intervention (H_2_GO!) was associated with 6-month reductions in child zBMI and 6-month reductions in SSB intake and increases in water intake among children and parents [36].

The goals of this study are to test the efficacy of H_2_GO! among an ethnically diverse sample of youth through a cluster randomized controlled trial (parallel group) and measure empowerment as a mediator. We partnered with Massachusetts Allianc of Boys and Girls Clubs of America (BGCs) to develop and pilot test H_2_GO! [37]. BGCs are an ideal partner for this proposal due to their commitment to empowering youth to lead healthy lives and their potential to reach large segments of our target population (4 million school-age youth; 56% low-income) nationally. We hypothesize that child participants in the intervention sites will have reduced zBMI and reduced SSB intake compared to child participants in the comparison sites and that the intervention effect(s) will be mediated by youth empowerment. This paper describes the design and methods for the cluster randomized controlled trial of the H_2_GO! intervention.

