### Statistical approach and power

Our sample size calculations (*N* = 45 parent-child pairs per each of the 10 sites) are based on the primary hypothesis that child participants in intervention sites will have reduced zBMI compared to child participants in comparison sites over 12 months. Our pilot study showed an effect size of 0.22 zBMI units over 6 months [36]. We powered our analysis to detect a minimum effect size of 0.1 units over 12 months (a conservative approach considering possible attenuation of effects over the doubling of study time period) and anticipate a 0.15 SD in both groups. A 0.1 effect size is reasonable for populations inclusive of healthy weight children; of studies targeting school-aged children including those of healthy weight, randomized SSB interventions have yielded 0.0–0.13 unit differences in zBMI over 12–18 months [62, 63], and childhood obesity prevention interventions have yielded 0.10–0.16 unit differences in zBMI over 12 months [64, 65]. We assume an intra-class correlation coefficient of 0.05 [66–68]. With α = 0.05 and a 75% retention rate, we can detect ≥0.1 unit difference in zBMI with over 80% power and 0.2 unit difference with over 90% power by enrolling a total of 450 parent-child pair participants.

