To test our secondary hypothesis that children in intervention sites will have decreased SSB intake and increased water intake than children in control sites over 12 months, we propose to compare SSB and water intake using linear mixed models and similar approaches described in the primary hypothesis testing. Comparisons of group mean changes from baseline to 2 and 6 months will also utilize this approach. We will additionally examine changes in child self-efficacy, parental beverage intake, SSB home availability, and spontaneous changes in other BMI-related behaviors (other dietary intake, physical activity, screen time, sleep) over time and by study condition using methods described above. Finally, for our mediation hypothesis, we will first examine whether the pattern of change in youth empowerment over time differs by study condition via a statistical interaction using a linear mixed model. Next, we will examine whether patterns of change over time in primary and secondary outcomes depend on level of empowerment by incorporating an empowerment by time interaction. Finally, we will incorporate both interaction terms (study condition by time and empowerment by time) to determine if the intervention effect is partially or fully mediated by empowerment.

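### The planned verdict of partial or full mediation should be replaced by direct and indirect effects with intervals, because at the planned effect size the trial cannot support a claim of full mediation

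*Protocol article*

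**What the plan says.** The Background section makes mediation a hypothesis of the trial: "the intervention effect(s) will be mediated by youth empowerment". The Planned statistical analysis section sets out three steps. The first tests whether change in empowerment differs by condition. The second tests whether change in the outcomes depends on empowerment, through an empowerment-by-time term. In the last step "we will incorporate both interaction terms (study condition by time and empowerment by time) to determine if the intervention effect is partially or fully mediated". The article gives no rule for telling partial from full, and it does not name the direct effect, the indirect effect or an interval for either.

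The Statistical approach and power section sizes the trial for the total effect on zBMI only: "We powered our analysis to detect a minimum effect size of 0.1 units over 12 months". It adds that "we can detect ≥0.1 unit difference in zBMI with over 80% power and 0.2 unit difference with over 90% power".

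**The concern.** To say that an effect is fully mediated is to say that nothing passes by another route. That is a claim of absence, and it needs an estimate precise enough to rule out a direct effect that matters. The article promises the verdict from a single joint model and names no such estimate.

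The three-step sequence is most naturally completed by calling mediation full when the condition-by-time term is no longer significant beside empowerment, and partial when it still is. Under that rule a failure to detect a direct effect is taken as proof that there is none. The intervention has other plausible routes to zBMI, such as the health sessions, the water bottle, the tracking and goal-setting sheets and the take-home activities with parents. Readers could be told that empowerment explains everything when a good part of the effect came by those routes.

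**Working it through.** **Inputs from the article** (Statistical approach and power; Study design): 10 clubs, 5 per arm; 45 pairs per club; 75% retention, so 45 × 0.75 = 33.75 per club; SD 0.15 ("anticipate a 0.15 SD in both groups"); ICC 0.05; α = 0.05; planned effect 0.1 zBMI.

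**Assumptions not in the article:** the test is two-sided; the SD and ICC apply to 12-month change; the t version uses 10 − 2 = 8 degrees of freedom, ignoring strata.

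**Step 1: the plan's own figure.**
- Design effect: 1 + (33.75 − 1) × 0.05 = 2.6375.
- Effective number per arm: 5 × 33.75 / 2.6375 = 63.98.
- Standard error: 0.15 × √(2 / 63.98) = 0.0265.
- Power for 0.1: 96.5% (normal) or 90.8% (t, 8 df). Power for 0.2: above 99.9%.

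The stated powers, over 80% and over 90%, are lower bounds and both hold.

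**Step 2: precision for the direct effect.** I use the same standard error as an approximation. Adjusting for empowerment removes some residual variance but adds collinearity with condition.
- 95% half-width: 1.96 × 0.0265 = 0.052 (normal), or 2.306 × 0.0265 = 0.061 (t, 8 df).
- This is 52% to 61% of the planned 0.1. An interval centred on zero would still contain 0.05.

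**Step 3: missing a direct effect of 0.05 (half of 0.1).**
- Standardised effect: 0.05 / 0.0265 = 1.885.
- Power is 47% (normal) or 38% (t, 8 df), so the term is non-significant 53% or 62% of the time.

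**Step 4: sensitivity to the total effect, half of it direct.**

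| Total effect | Normal | t, 8 df |
|---|---|---|
| 0.10 | 53% | 62% |
| 0.13 | 31% | 42% |
| 0.16 | 15% | 25% |
| 0.22 (pilot) | 1% | 5% |

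At a total of 0.1, other ICC values give (normal / t) 14% / 24% at ICC 0, 24% / 35% at 0.01, and 68% / 74% at 0.10.

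**Step 5: simulation.** The model was a linear mediation model for 12-month change: 10 clubs of 34 children, total effect 0.1, half of it direct. The article gives no expected shift in empowerment, so its size is assumed.
- Given a significant total effect, and shifts of 0.5 to 1.5 SD, the direct term is non-significant in 50% to 58% of runs with club-level inference. The figure is 13% to 35% if the analysis ignores clustering of change.
- In a separate simulation that also required both mediator paths to be significant, with shifts of 0.5 to 1.0 SD, the figure is 28% to 50% (normal) or 40% to 64% (t, 8 df).

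**Step 6: does lost precision favour a report of full mediation?** Further runs with 10, 8 and 6 clubs gave these rates of a significant total effect followed by a non-significant direct term:
- Given a significant total effect: 63%, 71%, 84%.
- Among all trials: 60%, 59%, 46%.

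**The case against.** The strongest objection is that the article states no significance rule. The team could compare coefficients with and without empowerment, and a statistical analysis plan that is not shown could define the criterion. A condensed article may leave estimators and intervals to that document. This stands as far as the rule is concerned: a reader might infer that the plan adopts loss of significance as its test, but the text does not say so. It does not remove the point, because the article itself fixes the outcome of the analysis as a two-way verdict. The half-width in step 2 limits any route to the word full at the planned effect.

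A second objection is that the 53% to 62% does not describe the planned model. That model has participant and site random intercepts, with no stated term for club-level variation in change and no stated 8-df test. This also stands in part. With intercepts only, the 13% to 35% range is the closer match. Those lower rates come from an analysis that leaves clustering of change out of the standard error although the simulated data contain it.

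A third is that the rate depends on effect size and falls to 1% to 5% at the pilot's value ("Our pilot study showed an effect size of 0.22 zBMI units over 6 months"). That is correct. However, the trial is planned on 0.1 because attenuation is expected.

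A reader might also infer that losing clubs or children makes a report of full mediation more likely overall. Step 6 does not support that. Noise also removes the significant total effect that there would be to mediate.

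**Conclusion.** The point holds in a limited form. The article commits to a verdict of partial or full mediation from one joint model and names no direct or indirect effect to support it. At the planned total effect of 0.1 zBMI, the 95% half-width of 0.052 to 0.061 means that even a direct estimate of zero leaves about half the planned effect unaccounted for.

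If non-significance is the rule, a direct effect of 0.05 is missed 53% (normal) to 62% (t, 8 df) of the time. The rate is about 13% to 35% if clustering of change is ignored, and 1% to 5% at a total of 0.22. Given a significant total effect, lower precision makes a false verdict of full mediation more likely, but it does not raise the unconditional chance of that report.

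These figures rest on a two-sided test, SD 0.15 and ICC 0.05 for change, an assumed empowerment shift in the simulations, and no unmeasured confounding of empowerment and outcome. The cause is low precision from few clubs combined with the ICC, not the number of clubs alone. The stated power for the total effect is correct. This is a modest point about a secondary, mechanistic analysis, and the primary efficacy conclusion is not affected.

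**What to change.** In the last step of the mediation analysis (Planned statistical analysis), replace the partial-or-full verdict with estimates of the direct and indirect 12-month effects on zBMI. Give each a 95% confidence interval that respects clubs, and interpret their sizes. Add a sentence saying that a non-significant direct effect does not by itself show full mediation.

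The cost is a change of wording and some interval estimation from data already being collected. The downside is that a claim of full mediation will rarely be available at this sample size.

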### Data safety monitoring board

Given the minimal risk involved, a full Data and Safety Monitoring Board was not deemed necessary. The PI and project team will be involved in ongoing monitoring of the trial and will meet annually to review study progress, data quality and safety.

### Dissemination plan

We plan to engage past study participants and community members in a series of community presentations regarding study results. We will post results in our project website, including study description, briefs with findings, and publications, as well as share findings to BGCs via newsletters, social media outreach, and local, regional, and/or national presentations. If the intervention is shown to be efficacious, we plan to create a dissemination package for our community partners that includes: manuals describing intervention components; procedures and resources for implementation and evaluation; staff training modules; and information regarding intervention feasibility and acceptability to inform adoption. Within the broader scientific community, we plan to submit study findings for presentation at national conferences and to publish study results in relevant peer-reviewed journals.

## Discussion

Reducing SSB intake is a critical target (and one of many needed) for childhood obesity prevention. The H_2_GO! intervention targets SSB intake through youth-produced narratives as a strategy to facilitate youth empowerment and parental engagement. The result is a novel SSB intervention that strategically engages youth in developing confidence, skills, and opportunities to affect their broader circumstances through cultivating and sharing their stories in the family and community settings. Our study also aims to measure youth empowerment as a mediator in the context of a childhood obesity prevention trial. Establishing this association will build further evidence of utilizing youth empowerment strategies to improve obesity-related behaviors and outcomes among youth.

We partnered with BGCs, a system of affordable afterschool care that reaches our target population (56% low-income; 33% White, 30% Black, 23% Hispanic) nationally [42]. BGCs are an ideal setting and leverage point for childhood obesity prevention programs, given that SSB intake and childhood obesity are major problems that have yet to be sufficiently addressed in this population and setting. The H_2_GO! intervention was designed in collaboration with BGCs for implementation through BGCs, a setting that has national reach and infrastructure to support our intervention model. The resulting H_2_GO! intervention aligns with the BGC goal of empowering youth to lead healthy lifestyles and has high potential for sustainability and dissemination.

## Data Availability

Not applicable.

## Abbreviations

BMI: Body mass index
BGC: Boys and Girls Clubs of America
ET: EmpowermentTheory
SSB: Sugar-sweetened beverages
zBMI: Body mass index z score
